## Abstract

**Introduction::**

Increasing continuity of care has been identified as a
strategy to improve patient outcomes, but previous studies of integrated care
have tended to focus on pilot areas, which limit their generalisability and the
ability to determine in which contexts integrated care was most successful.

**Objective::**

This study protocol describes a quantitative evaluation
of a reform in England that introduced named, accountable general practitioners
for all National Health Service (NHS) patients aged 75 years or over. The
national contract for general practice services required that named general
practitioners offer longitudinal continuity of care within the general practice
and be accountable for coordinating care to meet the patient’s healthcare
needs.

**Methods::**

This study will apply a regression discontinuity design to
pseudonymised electronic medical records from a sample of general practices in
England. We will compare outcomes for patients aged just below and above the age
of 75 to estimate the effect of named general practitioners and relate these
estimated treatment effects to the characteristics of general practices.
Outcomes will include a metric relating to continuity of care, namely the Usual
Provider of Care Index, and numbers of general practitioner contacts, referrals
to specialist care and diagnostic tests.

**Discussion::**

The study illustrates an approach to evaluate national
changes aimed at more integrated care using electronic records, which will
complement in-depth examination in pilot sites.

## Introduction

There has been a concerted effort in recent years to promote more integrated care in
England [1,2,3]. Integrated care is a term
often used to describe services that are coordinated around the patient and based
around their needs [1,2]. Continuity of care is an important part of this vision, and
patient satisfaction is strongly linked to the ability to see a doctor with whom the
patient has a personal relationship [4].
However, due to increased specialisation within primary care and the end of
‘personal registration’ with a particular general practitioner in the
last 10 years, there is concern that it is becoming more difficult for patients to
see their preferred general practitioner [5,6]. In England, 54% of patients
have a general practitioner they preferred to see, and this proportion is higher
among patients aged 75 and over, at 75% [7,8]. However, among adults with a
preferred general practitioner, 31% saw them only some of the time and 8% never or
almost never saw them in 2013/14 [9].

The term continuity of care has been used in a variety of ways and can encompass many
different ideas [10,11,12,13,14].
One model distinguishes between three related but distinct concepts: longitudinal
continuity of care with as few doctors or healthcare professionals as possible;
coordinated care, with good communication between professionals and a consistent
approach to the management of health needs; and the subjective experience of a
caring relationship [12]. There is evidence
that the various aspects are associated with positive effects on a range of
outcomes, including more appropriate prescribing and higher quality of life [14]. In particular, longitudinal continuity may
be an important element in interventions to reduce emergency department visits and
unscheduled hospital admissions [14,15,16].
Subjective continuity of care is strongly linked to patient satisfaction [4,10,17], which in turn may be a predictor of
compliance with following recommended treatments [14,18]. Although one study
reported that patients with a personal relationship with their general practitioner
experienced fewer referrals to specialist care than other patients [19], a retrospective cohort study suggested
more complex associations between longitudinal continuity and time to referrals and
diagnoses for certain cancers [20].

Many evaluative studies of the effect of interventions aimed at greater continuity of
care have been conducted within specific localities, which can limit the
generalizability of study findings [4,16,17,21,22,23]. However, in 2014,
the Department of Health reformed the contract for general practices in England to
require that all patients aged 75 or over be appointed a named general practitioner
with specific responsibilities for care coordination [24]. This policy provides an opportunity to evaluate the effect
of a national initiative on continuity of care and so relates variation in
effectiveness to differences in the local context [25]. Although a recurrent concern with ‘top-down’ reforms is
that changes might not have the active buy-in of local practitioners [26], with few exceptions [27] these are seldom evaluated. This is an important gap in the
literature as contractual reform is one of the few policy-making levers that promise
direct impact.

Estimating the effect of interventions aimed at providing more integrated or
continuous care is often challenging because studies are typically not randomised
[21,28]. Thus, intervention and control groups might differ at baseline and,
unless outcomes are accurately adjusted for these differences, inferences can be
biased [29]. Studies often use regression
adjustment or propensity score matching, but these methods assume that all relevant
baseline characteristics have been observed, which may be implausible [30]. Regression discontinuity methods avoid
having to make this assumption and are appropriate where eligibility for an
intervention changes sharply at a predefined threshold [31]. The key insight is that patients just above and below the
threshold should have similar baseline characteristics. Therefore, any discontinuity
in the outcome variable at the threshold can be attributed to differences in the
treatments received. Regression discontinuity designs have been shown to replicate
the results of randomised controlled trials [32] and, although underutilised in health services research, are well
established in the economics literature [31,33,34].

The article describes the design of a regression discontinuity study to assess
whether the national policy to introduce named accountable general practitioners led
to changes in the longitudinal continuity of care and to relate these to the
characteristics of general practices.

## Methods

### Reform to the general medical services contract in England

The 2014/15 General Medical Services contract introduced a requirement for
general practices in England to offer patients aged 75 or over a named
accountable general practitioner, who should provide longitudinal continuity of
care within the general practice and be accountable for coordinating care to
meet the patient’s health and social care needs. In particular, the named
accountable general practitioner should ensure that patients receive all
appropriate services and work with relevant associated healthcare and social
care professionals to deliver a multidisciplinary care package [24,35]. The contract requires that the practice notify the patient of their
named accountable general practitioner, usually by letter, and make a reasonable
effort to accommodate patient preferences about the choice of general
practitioner. However, patients are not prevented from seeing any other general
practitioner in the practice [36]. The
2014/15 GMS contract changes led to a step change (discontinuity) in the
percentage of patients receiving a named accountable general practitioner, which
increases from around 5% to around 80% near age 75 (Table 1).

**Table 1 T1:** Preliminary analysis of data from Clinical Practice Research Datalink
showing that the requisite discontinuity exists in the data.

	Patients aged 70–74 (%)	Patients aged 75–79(%)

Notified of named accountable general practitioner	5420 (5%)	67,770 (80%)
Not notified of named accountable general practitioner	99,830 (95%)	17,161 (20%)
Total	105,250	84,931

*Note:* Based on preliminary analysis of Clinical
Practice Research Datalink data. Figures are illustrative as this
analysis was based on 2014 data and not all exclusion criteria were
applied.

### Study design

Within a regression discontinuity design (illustrated in Figure 1), a step change in outcome at the threshold
is attributed to a difference in the treatments received on either side of the
threshold. The regression discontinuity design requires much weaker (and hence
more plausible) assumptions than other methods, such as regression adjustment,
which require that confounders are observed [31,37]. An important
assumption underlying all regression discontinuity designs is that, in the
absence of an intervention, outcomes will vary smoothly with the running (or
treatment determining) variable [31].
Thus, although older people might see their general practitioner more often than
younger people, contact rates should not be discontinuous at age 75 in the
absence of the introduction of named accountable general practitioners. The
assumption seems reasonable and can be validated, for example by ensuring that
there are no discontinuities in other covariates at age 75. The standard
regression discontinuity design estimates a ‘local treatment
effect’, which in our case will apply to patients aged 75. However,
preliminary analysis shows that, contrary to the eligibility rules, some
patients aged below 75 received a named accountable general practitioner, while
some older patients might not (Table 1).
As a result, we will apply a ‘fuzzy’ regression discontinuity
design, so our treatment effects will additionally apply only to patients who
are compliers, i.e. to patients who would receive a named accountable general
practitioner if eligible for one, but not otherwise.

**Figure 1 F1:**
[figure not shown]
Illustration of regression discontinuity design. Note: Hypothetical data to show the principles of the regression
discontinuity design.

### Study cohorts

All general practices in England were mandated to participate in the policy. We
will examine data from the electronic medical record of a national sample of
general practices that participate in the UK-wide Clinical Practice Research
Datalink. This is a validated and widely used research database that contains
anonymised, person-level clinical data for all registered patients, linkable to
other data sources, such as death records from the Office for National
Statistics and Hospital Episode Statistics administrative data [38].

We will study all English general practices that have submitted data to Clinical
Practice Research Datalink for the full 2014/15 financial year, excluding
practices for which data are identified by Clinical Practice Research Datalink
as not being up to research standard or that did not give permission for data
linkage. This is expected to result in approximately 200 practices. Within these
practices, we will study registered patients born between 1929 and 1949, and
thus aged between 65 and 85 in 2014. Patients will be excluded if they have
missing year of birth or gender, deregistered within the study period or were
identified as at high risk and started admission avoidance care, as part of the
Avoiding Unplanned Admissions Enhanced Service. All patients on the Service
received named accountable general practitioners irrespective of their age,
meaning that a regression discontinuity design is not appropriate for these
patients.

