## Statistical methods

Our initial analysis (Table 1) suggests that
the proportion of patients receiving a named accountable general practitioner is
discontinuous at the threshold, but this will be confirmed on receipt of the data.
We will also confirm that, although we would expect a trend in certain covariates
across age, there are no discontinuities in these covariates at age 75. This
comparison will be done graphically and include all patients, regardless of actual
treatment assignment. We do not expect such discontinuities to occur, but if they do
exist, this would lead us to question the validity of our study design.

As mentioned previously, the proportion of patients receiving a named accountable
general practitioner is unlikely to jump from 0 to 100% at age 75. It will therefore
be appropriate to apply a fuzzy regression discontinuity design [31], by fitting four regression models. Two
models will relate the outcome to a polynomial function of age: one model will be
fitted for people whose age lies within the bandwidth below the threshold and the
other model for people within the bandwidth above the threshold. The final two
models have treatment assignment as their dependent variable rather than outcome.
All models will use ordinary least squares regression and include patients
irrespective of their actual treatment assignment. We will calculate the estimated
treatment effect as the difference between the predictions of the two outcome models
at age 75, divided by the difference between the predictions of the two treatment
models at age 75.

The analysis will have regard to the rounded nature of the running variable (i.e.
age), resulting from the use of year of birth rather than full date of birth. This
will exclude the use of very small bandwidths, and so we will use a larger interval
spanning several years and model any trend in the endpoints by age using parametric
approaches based on polynomial functions [42,43]. In the absence of
information on full date of birth, it will not be possible to establish for a given
patient born in 1939 what date they turned 75, and therefore which side of the
threshold the patient is at the index date. We will remove the risk of
misclassification by excluding all patients born in 1939 when fitting the regression
models and making a small extrapolation around age 75 [42]. A final consideration is that, when the running variable
is only observed at discrete points, discretisation bias can occur because a change

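### Two exclusions, leaving the list and starting admission-avoidance care, are not limited to events before eligibility, and no check for a jump in either at age 75 is stated

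*Protocol article*

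**What the plan says.** The exclusion list in Study cohorts opens with "missing year of birth or gender, deregistered within the study period or were". Its last item is the group "identified as at high risk and started admission avoidance care, as part of the" national scheme against unplanned admissions. The deregistration rule covers the whole study period. The service rule carries no date.

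A reason is given for the second rule only. Service patients are said to have "received named accountable general practitioners irrespective of their age". The article states its inference from this as "meaning that a regression discontinuity design is not appropriate for these" people.

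Study design adopts a fuzzy design because certain "patients aged below 75 received a named accountable general practitioner, while" others above that age may have gone without. The effect is therefore limited to those who "are compliers, i.e. to patients who would receive a named accountable general" practitioner when eligible and in no other case. Statistical methods keeps patients in all four models whatever treatment they received. It defines the "treatment effect as the difference between the predictions of the two outcome models", taken where the two sides meet and scaled by the matching difference from the two treatment models.

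Strengths and limitations adds a second consideration. The results will not cover the 2% of the population at highest risk, because that group is receiving a more intensive intervention that calls for its own evaluation.

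**The concern.** A regression discontinuity compares like with like at the threshold only if membership of the analysis set does not itself change there. Treatment receipt is recorded from April to September 2014 and followed for 6 months (Exposure variable and index dates). As written, both rules can therefore remove a patient for something that happened after the named practitioner was assigned.

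Both events could depend on treatment. Under the contract the named practitioner must see that patients get the services they need and must work with others on a multidisciplinary package. Entry to a high-risk care programme could plausibly follow from that, and a closer link with one practitioner could affect whether a patient stays on the list.

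If the excluded share jumps at 75 and excluded patients use the practice more or less than others, the retained means differ across the threshold with no effect of treatment on contacts. The estimator cannot separate that difference from a treatment effect, and it divides it by the first stage, which enlarges it.

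The planned checks meet this only in part. The covariate check is graphical and is described for covariates, not for exclusion rates. Placebo cut-offs cannot show selection that is specific to 75.

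**Working it through.** **Inputs from the article.**
- Mean contacts without a named practitioner: 5 per 6 months. Meaningful change: 5% (Required sample size). Target = 0.05 × 5 = 0.25 contacts.
- First stage (Table 1): 67,770/84,931 = 79.8% and 5,420/105,250 = 5.1%, a jump of about 0.75. The article calls these figures illustrative, with not all exclusions applied.

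**Inputs assumed, because the article does not give them.**
- Excluded share just below 75: e = 3% or 5%.
- Gap g between the mean contacts of excluded patients and of retained patients below 75: 5 or 10.
- Jump d in the excluded share at 75: 0.25 to 2 percentage points.

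**Step 1. Does treatment irrespective of age require exclusion?** Let service patients be a share a on both sides of 75, all treated, with the same mean outcome on both sides. Let τ be the complier effect among the rest.
- Outcome jump: (1 − a) × 0.75 × τ. The service patients' contribution is equal on both sides and drops out.
- Treatment jump: [a + (1 − a) × 0.80] − [a + (1 − a) × 0.05] = (1 − a) × 0.75.
- Ratio: τ.

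With τ = 0.25 the ratio is 0.25 whether they are kept or removed. Keeping them only lowers the first stage from 0.75 to 0.735 (a = 2%), 0.7125 (5%) or 0.675 (10%). The article already keeps other under-75s who have a named practitioner, and the fuzzy design deals with them in this way.

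**Step 2. What if the excluded share jumps at 75?** Hold the underlying population the same on both sides, with an excluded share e below and e + d above. The retained mean above 75 then shifts by

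shift = −g × d / (1 − e − d), and bias in the complier effect = shift / 0.75.

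Example: e = 0.05, g = 5, d = 0.01. Shift = −0.05/0.94 = −0.053; bias = −0.053/0.75 = −0.071, or 28% of 0.25.

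| Jump d | e = 3%, g = 5 | e = 3%, g = 10 | e = 5%, g = 5 | e = 5%, g = 10 |
|---|---|---|---|---|
| 0.25 points | −0.017 | −0.034 | −0.018 | −0.035 |
| 0.5 points | −0.035 | −0.069 | −0.035 | −0.071 |
| 1 point | −0.069 | −0.139 | −0.071 | −0.142 |
| 2 points | −0.140 | −0.281 | −0.143 | −0.287 |

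The range is about −0.02 to −0.29 contacts, or 7% to 115% of the target. The base share hardly matters; the jump and the gap drive the result. A gap of 2.5 would halve the g = 5 columns. If the excluded share fell at 75, the sign would reverse.

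**Step 3. Would the covariate plots show it?** Prior contacts are among the covariates. If they carried the same gap, a 1-point jump would move their retained mean by about 0.05 (g = 5) to 0.11 (g = 10). On a mean near 5, a shift of that size is hard to see in a plot.

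**The case against.** **The cancelling argument and the bias argument need opposite conditions.** Service patients cancel only if their share is smooth at 75, and in that case excluding them does no harm either. If their share jumps, keeping them does not make them cancel, and the estimate then takes in whatever the more intensive service does. This stands. A reader might infer that the service exclusion is a mistake and that these patients belong in the main analysis. The article does not support that. Keeping them is a trade-off, and Strengths and limitations declares the restricted population and gives a defensible reason for it. The Study cohorts sentence is also true of the service group taken alone, since that group has no first stage at 75. It is only insufficient as a reason to remove the group from a fuzzy analysis.

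**The figures behind the size are all assumed.** This stands too. The only related number in the article is the 2% highest-risk group, which limits how far service entry could jump. High use is plausible for patients labelled high risk, but nothing in the article says it of people who leave the list. Patients tipped into the service at the margin may be less extreme than the rest. A reader might infer from the table that the primary result will be biased; the documents show only that it could be.

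**The covariate checks address this mechanism.** They do in part. Prior contacts, referrals, hospital discharges and long-term conditions are all examined, and a covariate-adjusted analysis is planned. Step 3 shows why a graphical check may still miss a shift that matters here.

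**Cohort dating may sit in the full protocol.** That is possible for service start, which the article leaves undated. It does not answer the deregistration rule, which the article sets over the study period.

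**Conclusion.** The point holds as a risk of selection at the threshold. Neither exclusion is tied to status before eligibility, both events could respond to treatment, and no stated check uses exclusion as an outcome. If both rates are smooth at 75, the exclusions do no harm to the comparison.

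The size cannot be known from the article. Under the assumed inputs, a jump of a quarter of a point with a gap of 5 contacts is minor (about 7% of the target). A 1-point jump costs about 28% to 57% of it, and a 2-point jump with a gap of 10 exceeds it. The study is designed to detect a 5% change, so it should show that the excluded share does not jump at 75.

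The service exclusion may stay on the ground given in Strengths and limitations. Treatment at any age is not a sufficient reason for it in a fuzzy design.

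**What to change.** 1. Define both exclusions by status before eligibility (1 April 2014) where the data allow.
2. Run the planned jump model at 75 with deregistration and with service entry, each in turn, as the dependent variable, on the cohort before these exclusions. Report both estimates with confidence intervals.
3. Add a sensitivity analysis that retains these patients, counting leavers' contacts up to exit with registered time taken into account.
4. If the sponsor prefers the restricted population, keep the service exclusion in the main analysis and rest it on the separate, more intensive intervention.

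Cost: revised cohort wording and a few extra runs of models already planned. The sensitivity analysis will have a slightly smaller first stage (0.735 in place of 0.75 if service patients are 2%) and more outcome variance. Its time-adjusted count differs from the declared endpoint of contacts per head over 6 months, which is a reason to keep it as a sensitivity analysis.

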### Exposure variable and index dates

For reasons of patient confidentiality, Clinical Practice Research Datalink
contains year of birth rather than full date of birth. Therefore, age will be
calculated by subtracting the year of birth from 2014, and we will compare
patients whose age was in a small bandwidth (interval) above and below 75 years.
This bandwidth will be selected using standard cross-validation methods [31].

We will report the proportion of patients in each age group who received the
intended treatments. Since the policy ensures that the vast majority of patients
who are eligible for a named accountable general practitioner within 2014/15
will have received one by September 2014, treatment receipt will be based on the
presence of a recorded named accountable general practitioner within a 6-month
period (April 2014 to September 2014), using the Read code prescribed by the
General Medical Services contract (67DJ). Patients without a recorded named
accountable general practitioner by September 2014 will be regarded as untreated
patients, even if they received a named accountable general practitioner
subsequently.

All patients will be assigned an index date for the purposes of calculating
endpoints and covariates. For patients who are assigned a named accountable
general practitioner between April and September 2014, this will be the date at
which this was recorded. Patients who are not assigned a named accountable
general practitioner during this period will be randomly assigned an index date,
such that the distribution of index dates across months is the same as for those
patients who did receive one. Thus, all patients will have at least 6 months
follow-up within 2014/15, before the policy was extended to all patients
irrespective of age [39].

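### A missing notification code is counted as no named GP, so the complier effect would be overstated to the extent that named GPs were given but not coded; the protocol gives no check or bound for this

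*Protocol article*

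**What the plan says.** Exposure variable and index dates defines receipt as a record of Read code 67DJ between April and September 2014. Patients with no such record are handled by a fixed rule: "Patients without a recorded named accountable general practitioner by September 2014 will be regarded as untreated patients". Anyone first coded after that window is classed in the same way. The six-month window is justified by an argument that opens "Since the policy ensures that the vast majority of patients who are eligible for a named accountable general practitioner within 2014/15" and concludes that these patients will have one by September 2014.

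The section on the contract reform describes two duties: to give the patient a named accountable GP, and to tell the patient who it is. Table 1 labels its rows by the second duty. The uncoded row is headed "Not notified of named accountable general practitioner" and holds 17,161 of 84,931 patients aged 75-79.

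Study cohorts states that "All general practices in England were mandated to participate in the policy". It excludes practices on data completeness, research standard and linkage permission, but not on use of the code.

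Statistical methods sets the estimate as the outcome jump "divided by the difference between the predictions of the two treatment models at age 75". The additional checks are placebo cut-offs, bandwidth, polynomial order and covariates.

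**The concern.** The rule makes absence of a code the same as absence of treatment. The protocol's own account gives some reason for doubt. The policy was mandatory and receipt by September is expected to be nearly complete, yet one in five patients aged 75-79 lacks a record that Table 1 describes as notification.

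The Study design section reads this gap as non-receipt and answers it with a fuzzy design. That works only if eligibility affects the outcome solely through the treatment as measured. A patient over 75 who has a named GP but no code may change the outcome jump while leaving the receipt jump as it was, and the ratio is then too large in absolute size.

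None of the planned checks would show this, because the error lies in the denominator. The limitations discuss recording quality only for staff logins and the Usual Provider of Care index. At stake is the size and meaning of the headline effect, which is presented as the effect of having a named GP among compliers.

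**Working it through.** **Inputs (Table 1).** Ages 70-74: 5,420 coded and 99,830 uncoded, total 105,250. Ages 75-79: 67,770 coded and 17,161 uncoded, total 84,931.

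**Table 1 reproduced.** 5,420/105,250 = 0.0515 and 67,770/84,931 = 0.7979, matching the printed 5% and 80%. The coded jump is J = 0.7979 - 0.0515 = 0.7464. The uncoded share above 75 is 1 - 0.7979 = 0.2021.

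**Overstatement.** Let u be the share of uncoded patients aged 75-79 who in fact have a named GP and experience its full effect. The documents do not give u, so it is an assumption running from 0 to 1. With the under-75 share held at 0.0515, the ratio is too large by

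factor = (J + 0.2021u) / J

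| u | Factor | A true 0.25 contacts (5% of 5) reads as |
|---|---|---|
| 0 | 1.00 | 0.25 |
| 0.25 | (0.7464 + 0.0505)/0.7464 = 1.068 | 0.267 |
| 0.5 | (0.7464 + 0.1010)/0.7464 = 1.135 | 0.284 |
| 1 | 0.9485/0.7464 = 1.271 | 0.318 |

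If uncoded patients respond only in part, the excess shrinks in proportion. With all of them holding a named GP but showing half the effect, the factor is again 1.135. If codes are missed equally often on both sides of 75, the extreme is 1/0.7979 = 1.253.

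**Why 1.27 is not a strict ceiling.** Table 1 is labelled illustrative, does not apply all exclusions, and compares five-year bands rather than predictions at 75. If only 75% or 70% of those above 75 were coded by September (assumed values), the extremes become 0.9485/0.6985 = 1.36 and 0.9485/0.6485 = 1.46.

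**Practices with little or no coding.** The documents give no practice-level rates, so the shares below are assumptions. There are two separate cases.

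- *They truly assigned no named GPs.* There is no bias, only lost precision. If such practices hold a share f of patients, keeping them multiplies the standard error by sqrt(1-f)/(1-f) = 1/sqrt(1-f). That is 1.054 at f = 10% and 1.118 at f = 20%.
- *They assigned named GPs but did not code them.* The estimate and its standard error are scaled up together. A simulation with f = 16% and a true effect of 0.25 (two groups, no age trend or clustering) gave 0.295 (SE 0.078) keeping them and 0.249 (SE 0.073) dropping them. Dropping removes the bias, but the estimate/SE ratio falls from 0.295/0.078 = 3.8 to 0.249/0.073 = 3.4.

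**Lower bound on the size of the effect.** Receipt above 75 cannot exceed 1, so the largest possible receipt jump is 1 - 0.0515 = 0.9485. Take a true effect of 0.25. If u = 1, the outcome jump is 0.25 × 0.9485 = 0.237, and 0.237/0.9485 returns 0.25. If u = 0, the outcome jump is 0.25 × 0.7464 = 0.187, and 0.187/0.9485 = 0.197. The bound does not exceed the true size in either case.

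**High-recording practices.** With at least 90% coded above 75 and about 5% below, the factor is at most 0.95/0.85 = 1.12.

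**The case against.** The strongest reply is that nothing in the documents shows under-coding rather than non-receipt. A vast majority is compatible with 80%. The code is the one that the contract prescribes, and Study design already allows that some older patients received no named GP. Notification is also part of the intervention: the endpoints section names the letters as a possible route to more contacts. Patients never told of their named GP may therefore show little or no effect, and little bias would follow. All of this stands, and it is why the size can only be given as a range starting at zero.

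A reader might infer that some practices hardly used the code and should be removed from the primary analysis. The documents do not support this: they only fail to exclude such practices. Exclusion at a chosen threshold would be arbitrary. It would narrow a sample whose national coverage is a stated strength, and it would cost power if those practices had assigned named GPs. Bias and lost precision also belong to different situations and should not be added together.

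It can also be said that code-quality checks belong in a fuller document. That does not dispose of the point, because the article itself fixes the receipt rule, the practice exclusions and the divisor. Reporting receipt by age group and confirming the jump, both planned, describe the coded variable and cannot separate uncoded from untreated.

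**Conclusion.** The concern holds in conditional form. The protocol equates no code with no treatment and divides by the coded jump. Any named GP that was given but not coded, and that changed outcomes, inflates the complier effect. On Table 1 the overstatement runs from 0%, through about 7% and 14% at u = 0.25 and 0.5, to about 27% at u = 1 with full effect. The 27% is an extreme case from illustrative data, neither an expected value nor a firm ceiling, and it would be wrong to read it as the study's likely bias. The outcome jump and its test are not affected, so the evidence on whether the policy changed contacts stands. What is uncertain is the size of the effect per named GP. Any precision loss from practices that truly assigned none is modest (standard error about 5% higher at 10% of patients, 12% at 20%) and rests on assumed shares.

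**What to change.** Keep all eligible practices in the primary analysis and make four additions.

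1. Describe the pooled ratio as the effect per recorded notification, not per named GP.
2. Report the outcome jump at 75 alongside the ratio, since it does not depend on coding.
3. Give a lower bound on the size of the named-GP effect: the outcome jump divided by 1 minus the below-75 receipt share (about 0.95 on Table 1).
4. Pre-specify, using recording data only and blind to outcomes, a sensitivity analysis in practices with high recording among patients born 1929-1938, for example at least 90%. Include or exclude whole practices, on both sides of 75, so that the discontinuity comparison is preserved.

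A sentence in the limitations should say that an absent code may mean either no named GP or no record of one.

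The cost is some wording and two extra runs on data already held. The sensitivity run will rest on fewer and less representative practices, so it should inform the reading of the primary estimate and not replace it.
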